# GENERAL INFORMATION

This document describes the TaMoVac II trial and provides information about procedures for entering participants into it. Every care was taken in drafting the protocol, but corrections or amendments may be necessary. These will be circulated to the Principal Investigators in the trial, prior to implementation. Clinical problems relating to this trial should be referred to one of the Principal Investigators or the Medical Expert.

**ABBREVIATIONS AND GLOSSARY**

|               |                                                                                                                                                                                  |
|---------------|----------------------------------------------------------------------------------------------------------------------------------------------------------------------------------|
| Ab            | Antibody                                                                                                                                                                         |
| ADCC          | Antibody-dependent cell-mediated cytotoxicity                                                                                                                                    |
| AE            | Adverse event                                                                                                                                                                    |
| AIDS          | Acquired immunodeficiency syndrome                                                                                                                                               |
| ALT/AST       | Alanine aminotransferase and aspartate aminotransferase liver enzymes                                                                                                            |
| ALVAC-HIV     | Canary pox Avipox vectored HIV vaccine candidate (ALVAC-HIV)                                                                                                                     |
| APC           | Antigen-presenting cells                                                                                                                                                         |
| C             | Centigrade or Celsius                                                                                                                                                            |
| CBC           | Complete blood count                                                                                                                                                             |
| CD4+          | A functional subclass of T cells, helper T lymphocytes (Th) that are necessary for augmentation and coordination of innate and adaptive effector responses, humoral and cellular |
| CD8+          | Cytotoxic T-Cells that destroy host cells, which have become infected by viruses or other intracellular pathogens                                                                |
| CDC           | United States Centers for Disease Control and Prevention                                                                                                                         |
| CEFC          | Chick embryo fibroblast cells                                                                                                                                                    |
| CRC           | Clinical Research Coordinator                                                                                                                                                    |
| GMP           | Good Manufacturing Practices                                                                                                                                                     |
| CIOMS         | Council of International Organization of Medical Sciences                                                                                                                        |
| CISPOC        | Centro de Investigação e Treino em Saúde de Polana Caniço                                                                                                                        |
| CRF           | Case report form                                                                                                                                                                 |
| CRP           | C Reactive Protein                                                                                                                                                               |
| CTL           | Cytotoxic T lymphocyte                                                                                                                                                           |
| DAERS         | DAIDS Adverse Experience Reporting System                                                                                                                                        |
| DAIDS         | U.S. Division of AIDS, NIAID, -                                                                                                                                                  |
| DCAC          | Data Coordinating and Analysis Center                                                                                                                                            |
| DNA           | Deoxyribonucleic acid                                                                                                                                                            |
| DSMB          | Data and Safety Monitoring Board                                                                                                                                                 |
| ECG           | Electrocardiogram                                                                                                                                                                |
| EDTA          | Ethylenediaminetetraacetic acid                                                                                                                                                  |
| EAE           | Expedited Adverse Events                                                                                                                                                         |
| ELISA         | Enzyme linked immunosorbent assay                                                                                                                                                |
| ELISPOT       | Enzyme-Linked Immunospot                                                                                                                                                         |
| EP            | Electroporation                                                                                                                                                                  |
| Env           | Envelope                                                                                                                                                                         |
| FDA           | U.S. Food and Drug Administration                                                                                                                                                |
| FTA           | Fluorescent treponemal antibody                                                                                                                                                  |
| GCP           | Good Clinical Practices                                                                                                                                                          |
| GLP           | Good Laboratory Practices                                                                                                                                                        |
| HBsAg         | Hepatitis B surface antigen                                                                                                                                                      |
| HCM           | Hospital Central de Maputo                                                                                                                                                       |
| HIV and HIV-1 | Human immunodeficiency virus, type 1                                                                                                                                             |
| HLA           | Human leukocyte antigen                                                                                                                                                          |
| HVTN          | HIV Vaccine Trials Network                                                                                                                                                       |
| IAVI          | International AIDS Vaccine Initiative                                                                                                                                            |
| IB            | Investigator's Brochure                                                                                                                                                          |
| IC            | Imperial College of London                                                                                                                                                       |
| ICF           | Informed Consent Form                                                                                                                                                            |
| ICH           | International Conference on Harmonization                                                                                                                                        |
| ICS           | Intracellular cytokine staining                                                                                                                                                  |
| ID            | Intradermal injection                                                                                                                                                            |
| IgG           | Immunoglobulin G                                                                                                                                                                 |
| IM            | Intramuscular injection                                                                                                                                                          |
| IND           | Investigational New Drug Application                                                                                                                                             |

|               |                                                          |
|---------------|----------------------------------------------------------|
| INF- $\gamma$ | Interferon gamma                                         |
| INS           | Instituto Nacional de Saúde                              |
| IRB           | Institutional Review Board                               |
| LMU           | Ludwig-Maximilians University of Munich                  |
| LPA           | Lymphocyte proliferation assay                           |
| LSI           | Lymphocyte stimulation index                             |
| MH            | Muhimbili Hospital                                       |
| MHC           | Major histocompatibility complex                         |
| MHRP          | US Military HIV Research Program                         |
| mg            | Milligram                                                |
| mL            | Milliliter                                               |
| mm            | Millimeter                                               |
| MMRC          | NIMR-Mbeya Medical Research Center                       |
| MNH           | Muhimbili National Hospital                              |
| MO            | Medical Officer                                          |
| MRC CTU       | Medical Research Council Clinical Trial Unit             |
| MRH           | Mbeya Referral Hospital                                  |
| MUHAS         | Muhimbili University of Health and Allied Sciences       |
| MVA-CMDR      | Modified Vaccinia Ankara- Chiang Mai Double Recombinant  |
| NAb           | Neutralizing antibody                                    |
| NIAID         | National Institute of Allergy and Infectious Diseases    |
| NIMR          | National Institute for Medical Research                  |
| NYVAC         | New York Vaccinia Virus Strain                           |
| PBMC          | Peripheral blood mononuclear cells                       |
| PBS           | Phosphate buffered saline                                |
| PCR           | Polymerase chain reaction                                |
| pfu           | Plaque forming units (equivalent to International Units) |
| PI            | Principal investigator                                   |
| PIN           | participant identification number                        |
| PIR           | post-injection reactogenicity                            |
| rMVA          | Recombinant MVA                                          |
| RNA           | Ribonucleic acid                                         |
| RPR           | Rapid plasma reagin                                      |
| SADR          | Suspected adverse drug reaction                          |
| SAE           | Serious adverse event                                    |
| SC            | Subcutaneous injection                                   |
| SIV           | Simian immunodeficiency virus                            |
| SMI           | Swedish Medical Institute                                |
| SOE           | Schedule of Evaluations                                  |
| STEP          | HVTN 502/Merck 023 trial                                 |
| SUSAR         | Suspected unexpected serious adverse reaction            |
| TaMoVac       | Tanzania Mozambique Vaccine Trial                        |
| TB            | Tuberculosis                                             |
| TBD           | To be determined                                         |
| TFDA          | Tanzania Food and Drug Administration                    |
| TM01          | TaMoVac 01 Trial                                         |
| TM02          | TaMoVac 02 Trial                                         |
| TMG           | Trial Management Group                                   |
| TMT           | Trial Mananagment Team at each clinical centre           |
| UKHVC         | UK HIV Vaccine Consortium                                |
| UNAIDS        | The Joint United Nations Programme on HIV/AIDS           |
| U.S.          | United States                                            |
| VRC           | Vaccine Research Centre of the U.S. INS                  |
| VDRL          | Venereal Disease Research Laboratory                     |
| WB            | Western blot                                             |

|       |                                        |
|-------|----------------------------------------|
| WBC   | White blood cell count                 |
| WHO   | World Health Organization              |
| WRAIR | Walter Reed Army Institute of Research |

# 1 SUMMARY

## 1.1 Summary of trial design

### 1.1.1 Design

This is a randomised, three-centre, factorial design to assess a prophylactic HIV vaccine with the HIVIS DNA prime administered ID by the Zetajet® device with or without the Derma Vax™ electroporation device at a dose of 0.6mg in a concentration of 3mg/ml or in a concentration of 6mg/ml, followed by IM MVA-CMDR 10^8pfu per ml either alone or given at the same time as IM 100 µg CN54 rgp140 adjuvanted with 5µg GLA-AF.

Approximately 18 participants will be allocated to receive placebo. Clinical staff will not know who received placebo, but they cannot be blinded to the group, and will know whether the participant is allocated to electroporation, and receives one or two injections at each timepoint. Laboratory staff will be blind to the group and the allocation of placebo.

### Disease/participants studied

198 healthy, HIV uninfected volunteers, 18 to 40 years old who are at low risk of HIV infection will be recruited with 80 from Mbeya and 80 from Dar es Salaam, Tanzania and 38 from Maputo, Mozambique. A minimum of 50 females will be enrolled, and they will be evenly distributed between the three groups.

### 1.1.2 Trial interventions

The doses, formulations, routes and schedule of immunisation are described in Table 1 below.

**Table 1 Schedule of doses, formulation and routes of immunisation**

| Groups |                  | DNA prime
at weeks 0, 4, 12                         | MVA+/- CN54 rgp140/GLA-AFboost
at weeks 24 and 40                                                                                                   |
|--------|------------------|--------------------------------------------------------|--------------------------------------------------------------------------------------------------------------------------------------------------------|
| I      | A Vaccine (n=60) | A 2 inj. of 0.1mL DNA tot 600µg                        | A.1: 1x1 mL MVA 10  pfu IM and
1x0.4 mL [100 µg] CN54 rgp140/GLA-AF [5µg]
IM (n=30)
A.2: 1x1 mL MVA 10  pfu IM (n=30) |
|        | B Placebo (n=6)  | B 2 inj. of 0.1mL saline
ID Zetajet®                | B.1: 1x1 mL saline IM and 1x0.4 mL saline IM (n=3)
B.2: 1x1mL saline IM (n=3)                                                                       |
| II     | A Vaccine (n=60) | A 2 inj. of 0.1mL DNA tot 600µg                        | A.1: 1x1 mL MVA 10  pfu IM and
1x0.4 mL [100 µg] CN54 rgp140/GLA-AF [5µg] IM
(n=30)
A.2: 1x1 mL MVA 10  pfu IM (n=30) |
|        | B Placebo (n=6)  | B 2 inj. of 0.1mL saline
ID Zetajet® +Derma Vax™ EP | B.1: 1x1 mL saline IM and 1x0.4 mL saline IM (n=3)
B.2: 1x1mL saline IM (n=3)                                                                       |
| III    | A Vaccine (n=60) | A 1 inj. of 0.1mL DNA tot 600µg                        | A.1: 1x1 mL MVA 10  pfu IM and
1x0.4 mL [100 µg] CN54 rgp140/GLA-AF [5µg]
IM (n=30)
A.2: 1x1 mL MVA 10  pfu IM (n=30) |
|        | B Placebo (n=6)  | B 1 inj. of 0.1mL saline
ID Zetajet® +Derma Vax™ EP | B.1: 1x1 mL saline IM and 1x0.4 mL saline IM (n=3)
B.2: 1x1mL saline IM (n=3)                                                                       |

DNA will be given in **combined** plasmid pools: 1 injection ID of 0.1 ml of 3mg/ml the combined Pool 1 (env) and Pool 2 (gag) into the left and right arm (Groups I and II) or only into the left arm (Group III), 0.1 ml of 6 mg/ml.

### 1.1.3 Objectives

#### Primary objectives:

1. To compare the safety and immunogenicity of three different priming regimens of 600µg HIVIS-DNA administered to healthy HIV uninfected volunteers as:
  - a. Two 300µg injections (3mg/ml) ID via Zetajet® without Electroporation or
  - b. Two 300µg injections (3mg/ml) ID via Zetajet® followed by ID Derma Vax™ Electroporation or
  - c. A single 600µg injection (6mg/ml) via Zetajet® followed by ID Derma Vax™ Electroporation
2. To compare the safety and immunogenicity of boosting healthy HIV uninfected adult participants primed with HIVIS DNA with:
  - a. IM MVA-CMDR with IM 100µg CN54 rgp140 adjuvanted with 5µg GLA-AF or
  - b. IM MVA-CMDR alone

#### Secondary objectives:

1. To build expertise and capacity for the evaluation of HIV-1 vaccine candidates in Tanzania and Mozambique
2. To evaluate the perception, attitude and knowledge towards the TaMoVac vaccine trials within study participants and their social environment

### 1.1.4 Outcome measures

#### Safety

- Grade 3 or above local solicited adverse event (**Table 2**)
- Grade 3 or above systemic clinical and laboratory solicited adverse event (**Table 2**)
- Any grade of adverse event that results in a clinical decision to discontinue further immunisations
- Any grade of adverse event that occurs in a participant that has received at least one immunisation

**Table 2 Solicited adverse events**

|                                  |                                                                                                                                                               |
|----------------------------------|---------------------------------------------------------------------------------------------------------------------------------------------------------------|
| Local AEs
(immunisation site) | Local Pain
Local Itching
Warmth
Redness in cm
Swelling (soft) in cm
Induration (hard) in cm
Blisters (blood or clear) in cm
Papule in cm |
| Systemic Clinical AEs            | Temperature
Chills
Myalgia/flu-like general muscle aches
Aching joints
Malaise (excess fatigue)
Headache
Nausea
Vomiting                 |
| Systemic Laboratory AEs          | Creatinine, ALT, total and direct bilirubin, glucose
Hb, total WBC, neutrophils, lymphocytes, platelets                                                    |

## **Immunogenicity**

- The presence and breadth of IFN- $\gamma$  ELISpot responses to a pool of HIV-peptides encoded by the vaccine to which there was no response at baseline.
- The magnitude of IFN- $\gamma$ ELISpot responses as measured by the number of spot forming cells per million PBMCs in response to pools of HIV-peptides in the IFN- $\gamma$ Elispot assay.
- The presence of CD4+ and CD8+ T-cell cytokine responses to pools of HIV peptides assessed by ICS.
- The presence and endpoint titre of systemic CN54rgp140-specific IgG antibodies.
- The presence and endpoint titre of systemic IgG and IgA HIV-specific binding antibodies.
- The presence and endpoint titre of tier 1 and tier 2 neutralising antibodies.

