### 7.4.1 Cellular responses

The **primary immunogenicity endpoint** will be measured by a standard IFN- $\gamma$  ELISPOT assay using fresh PBMC and pools of overlapping peptides representing Env, Gag and Pol proteins. ELISPOT responses are considered positive if the numbers of spot-forming cells (SFC) are more than four times the background (RPMI medium only) and > 55 SFC per million PBMC (Merck definition). Quality control and exchange of specimens with international laboratories will be performed.

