### 9.2 Outcome measures

#### 9.2.1 Primary outcomes

##### 9.2.1.1 Immunogenicity

- The primary **immunogenicity** endpoint will be determined from the following results:
  - a positive response in the HIV peptide-specific  $\gamma$ -IFN Elispot assay using freshly isolated PBMCs collected 2 weeks after the final vaccination. A positive result will be defined as the numbers of spot-forming cells (SFC) more than four times the background (RPMI medium only) and > 55 SFC per million PBMC (Merck definition)
  - the magnitude of the  $\gamma$ -IFN Elispot assay response which will be restricted to those samples which have been defined as positive, as measured by the SFC 2 weeks after the final vaccination
  - the endpoint titre or concentration of systemic IgG CN54rgp140 specific antibodies measured 2 and/or 4 weeks after the final vaccination
  - the presence of neutralising antibodies to tier 1 and tier 2 viruses and the titre when these are present

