### 9.5.2 Immunogenicity variables

IFN- $\gamma$  Elispot responses will be measured using freshly isolated PBMCs which will be purified from whole blood. Cells will be stimulated using pools of peptides derived from the vaccine and also negative and positive control stimuli. The number of spot-forming cells (SFC), indicative of IFN- $\gamma$  cytokine release will be enumerated using an automated Elispot reader. A positive result will be defined as numbers of spot-forming cells (SFC) more than four times the background (RPMI medium only) and > 55 SFC per million PBMC (Merck definition).

The proportion of CD4+ and CD8+ T-cells producing particular cytokines/chemokines and expressing cytolytic markers in response to HIV-1 peptides (as used in the Elispot assay) will be assessed. Frozen PBMCs will be used and thawed prior to analysis according to established methods. PBMCs will be stimulated *in vitro* and T-cell subsets and cytokine responses described using multi-parameter flow cytometry. Subsets of T-cells will be identified on the basis of the expression of cell surface markers and the percentages of CD4+ and CD8+ T-cells producing cytokines/chemokines will be determined with reference to the responses to control stimuli.

Binding antibodies with specificity for HIV antigens (Clade A, C and E) including those specific for the immunogen CN54rgp140 will be measured using standard ELISAs. ELISA absorbance readings for binding antibodies will be classified as 'response' or 'no response' using pre-defined cut-offs. Only samples with a detectable antibody response will be subjected to endpoint titration. In cases when a sample is positive for the presence of binding antibodies to CN54rgp140, the absolute concentration of antibody will also be determined. The concentration will be calculated relative to a commercially available standard purified antibody which will be titrated on the same plate as sample sera. Assays for the detection of neutralizing antibodies to HIV subtypes A, C and E will be performed using standardised assays including those using the TZMBL cell line and PBMCs.

All the immunogenicity endpoints will be signed off by the Laboratory Investigators. In the unlikely event that the Laboratory Investigators cannot reach consensus on a response, an expert Endpoint Panel will be assembled to make a final decision.

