Prior to the main analysis, the Statistical Analysis Plan will be finalised describing the methods for comparing the groups in detail. The decision to compare the proportion of responders, or the magnitude of response, and the definition for these parameters will be informed by the full analysis of TaMoVac 01 and the results of other relevant clinical trials, with the aim of defining a 'clinically meaningful result'. Proportions will be presented with a confidence interval and groups compared using Fisher's exact test. Response magnitude will be compared between groups using rank tests.

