# APPENDIX 1: STUDY TIMETABLE

| Target day | Week | Visit | Visit/Assessment type                          | Visit Window                  |
|------------|------|-------|------------------------------------------------|-------------------------------|
|            | -4-8 | V1    | Screening I                                    | 4-8 weeks before V3 enrolment |
|            | -2-4 | V2    | Screening II + baseline immunogenicity I       | 2-4 weeks before V3 enrolment |
| 0          | 0    | V3    | Enrolment + DNA I + baseline immunogenicity II | Week 0                        |
| 0          |      | V3A   | 30 min post vaccination                        |                               |
| 0          |      | V3B   | Evening of vaccination day                     |                               |
| 1          |      | V3C   | Day 1 post vaccination                         |                               |
| 2          |      | V3D   | Day 2 post vaccination                         |                               |
| 3          |      | V3E   | Day 3 post vaccination                         |                               |
| 4          |      | V3F   | Day 4 post vaccination                         |                               |
| 5          |      | V3G   | Day 5 post vaccination                         |                               |
| 6          |      | V3H   | Day 6 post vaccination                         |                               |
| 7          |      | V3I   | Day 7 post vaccination                         |                               |
| 14         | 2    | V4    | Follow-up safety (+ immunogenicity)            | 14 days post V3 +/- 3 days    |
| 28         | 4    | V5    | DNA II + Follow-up safety                      | 28 days post V3 +/- 3 days    |
| 28         |      | V5A   | 30 min post vaccination                        |                               |
| 28         |      | V5B   | Evening of vaccination day                     |                               |
| 29         |      | V5C   | Day 1 post vaccination                         |                               |
| 30         |      | V5D   | Day 2 post vaccination                         |                               |
| 31         |      | V5E   | Day 3 post vaccination                         |                               |
| 32         |      | V5F   | Day 4 post vaccination                         |                               |

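### The baseline condition on an ELISpot response in section 1.1.4 is missing from the primary outcome, so reactivity already present at enrolment would count as vaccine response

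*Protocol*

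**What the plan says.** The protocol describes the ELISpot response in two ways.

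- **With a baseline condition.** Section 1.1.4 (Outcome measures, Immunogenicity) lists the presence and breadth of IFN-γ ELISpot responses to a vaccine-encoded pool "to which there was no response at baseline".
- **Without one.** For the primary outcome at 2 weeks after the final vaccination, section 9.2.1.1 states: "A positive result will be defined as the numbers of spot-forming cells (SFC) more than four times the background", together with more than 55 SFC per million PBMC. Section 7.4.1 has the same rule: "ELISPOT responses are considered positive if the numbers of spot-forming cells (SFC) are more than four times the background", with the same second cut-off. Section 9.5.2 repeats it for the analysis variable. In all three, background means the medium-only wells of the same sample, not the participant's pre-vaccination sample.

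A baseline sample exists. Appendix 1 labels the week 0 visit "Enrolment + DNA I + baseline immunogenicity II", and Appendix 2 marks a fresh-cell ELISpot at that visit.

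Section 9.5.2 leaves the choice between proportion and magnitude to the SAP, "and the definition for these parameters will be informed by the full analysis of TaMoVac 01" and other trials. It does not mention the difference between 1.1.4 and 9.2.1.1.

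**The concern.** Take a participant whose cells react to one pool at enrolment and to that same pool, and no other, at week 42. Under 1.1.4 this is not a response. Under 9.2.1.1 the participant is a responder for the primary outcome. The two rules classify the same data differently.

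Three things depend on which rule applies.

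- **Attribution.** A reaction that predates the first injection would be reported as vaccine-induced.
- **The group comparison.** Randomisation balances baseline reactors across groups but does not remove them. They add positives everywhere, and more to the lower-responding group because more of its members would otherwise be negative. The difference therefore shrinks.
- **The magnitude and breadth outcomes.** Section 9.2.1.1 restricts the magnitude analysis to samples defined as positive, so the same rule decides who enters it. Section 9.2.2.1 makes breadth to gag a secondary outcome with no baseline condition, although 1.1.4 applies the condition to breadth as well.

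**Working it through.** **Inputs.** From section 9.3: 60 per group at alpha 2.5% (first randomisation), 90 per group at alpha 5% (second randomisation), and a target difference of 30 percentage points. From section 7.4.1: peptide pools representing Env, Gag and Pol. The protocol gives no baseline reactivity rate f, so f = 2%, 5% and 10% are assumptions.

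**1. The plan's own figure.** Two-sided normal formula with pooled variance under the null:

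power = Φ{ [ |p2 − p1| − z·√(2p̄(1−p̄)/n) ] / √([p1(1−p1) + p2(1−p2)]/n) }

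For 40% v 70%, n = 60, z = 2.241 and p̄ = 0.55: numerator 0.300 − 2.241 × 0.0908 = 0.0964; denominator √(0.45/60) = 0.0866; ratio 1.113; power 86.7%. The protocol states 86. For 50% v 80% the formula gives 89.8% (stated 89). With n = 90 and alpha 5% it gives 98.6% and 99.1% (stated 98 and 99). The table reproduces.

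**2. Effect of having no baseline condition.** Suppose a share f, equal in all groups and independent of vaccine response, is positive regardless of vaccine. Then

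observed rate = p + f(1 − p), so observed difference = (1 − f)(p2 − p1).

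| f (assumed) | Observed rates, true 40% v 70% | Difference (points) | Power, n=60, alpha 2.5% | Power, 50% v 80%, n=60 | Power, 40% v 70%, n=90, alpha 5% |
|---|---|---|---|---|---|
| 0 | 40.0 v 70.0 | 30.0 | 86.7% | 89.8% | 98.6% |
| 2% | 41.2 v 70.6 | 29.4 | 85.3% | 88.7% | 98.2% |
| 5% | 43.0 v 71.5 | 28.5 | 83.0% | 87.0% | 97.7% |
| 10% | 46.0 v 73.0 | 27.0 | 78.9% | 83.8% | 96.4% |

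For 40% v 70% at n = 60 the loss is 1.4 points at f = 2%, 3.7 at 5% and 7.8 at 10%.

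**3. How the condition is applied matters.** For 40% v 70%, n = 60, alpha 2.5%:

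- *Score every baseline reactor as a non-responder.* Rates become p(1 − f), so the difference shrinks by the same factor. Power is 85.0%, 82.2% and 77.2% at f = 2, 5 and 10%, slightly below the figures in step 2.
- *Remove every baseline reactor from the denominator.* The 30 points are kept with n(1 − f) per group. Power is 86.0%, 84.8% and 82.5%.
- *Drop only the reactive pool and assess the participant on the rest.* As an illustration, assume three equally responsive, independent pools and one reactive pool per baseline reactor. A reactor's chance of response on the other two is 1 − (1 − p)^(2/3), that is 28.9% where p = 40% and 55.2% where p = 70%. At f = 10% the group rates are 0.9 × 40 + 0.1 × 28.9 = 38.9% and 0.9 × 70 + 0.1 × 55.2 = 68.5%, a difference of 29.6 points and power of 85.6%. If responses to the pools are fully correlated, nothing is lost and power is 86.7%. Without the condition it is 78.9%.

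**The case against.** **The passages may be complementary.** Section 1.1.4 is a summary list that does not separate primary from secondary outcomes. The other three sections can be read as an assay cut-off for one sample, with 1.1.4 saying which pools count. This reading is possible, but 9.2.1.1 sets out the primary endpoint and its positive result in full, for a stated time point, and does not refer to 1.1.4. Someone programming from it would not use the baseline sample.

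**The SAP may settle it.** Section 9.5.2 defers the definition, and the SAP is not at hand. A reader might infer that the trial will analyse the outcome without a baseline condition. The protocol does not establish that; it is a risk. The deferral still leaves two stated rules unreconciled.

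**The rate is probably small.** Participants have a negative HIV antigen/antibody ELISA and are at low risk (section 4.1), and earlier recipients of an HIV candidate vaccine are excluded (section 4.2). This stands. It makes the lower part of the assumed range more plausible than 10%.

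**A baseline condition can cost power.** True if reactors are scored as non-responders, or if there is only one pool (77.2% against 78.9% at f = 10%). With several pools, and only the reactive pool dropped, most or all of the loss is recovered under the assumptions above. How much depends on the correlation between pools, which the protocol does not give.

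**It does not remove all false positives.** This also stands. A spurious positive that first appears at week 42 counts under either rule.

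**Conclusion.** The inconsistency is real and bears on the definition of a primary outcome. Without a baseline condition, pre-existing reactivity is counted as vaccine response: reported rates are too high and differences between groups are too small by the factor (1 − f).

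The size is modest and conditional. It assumes that background reactivity is equal across groups and independent of vaccine response, and it uses a rate the protocol does not report. At f = 2 to 5% the loss is about 1.4 to 3.7 power points for 40% v 70% with 60 per group. For the same rates with 90 per group at alpha 5% it is under one point (98.6% to 97.7% at f = 5%).

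A reader might conclude that the sample size is wrong or the trial underpowered for this reason. The protocol does not support that: its power figures reproduce, and none is wrong because of this point. Fisher's exact test, which section 9.5.2 plans, gives 81.4% rather than 86.7% for 40% v 70% at n = 60 even when f is zero; that gap comes from the test and has nothing to do with baseline.

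**What to change.** Carry the condition in 1.1.4 into 9.2.1.1, 7.4.1 and 9.5.2:

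- A responder meets the existing cut-offs 2 weeks after the final vaccination for at least one pool that was negative in the enrolment sample.
- A pool reactive at enrolment is dropped for that participant, who is still assessed on the remaining pools.
- A participant with no baseline-negative pool leaves the denominator and is not scored as a non-responder.
- The same rule decides which positives enter the magnitude analysis and which pools count towards breadth.

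The wording should also say how a missing enrolment result is handled, and it should be fixed before results by group are seen.

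The cost is a change of text. No new sample or visit is needed, because the enrolment ELISpot is already scheduled. Reported response rates will be slightly lower, and a few participants may not be evaluable for the responder outcome.
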